### Participants

The study has been approved by the GLA Institutional Review Board (IRB; PCC# 2014 -020159 2-12-14). An independent Data Safety Monitoring Board (DSMB), to which data on each subject will be submitted for review every three months for the first twelve months and then every six months for the last twelve months, has been established. The DSMB has already stipulated that the first subject be monitored for at least six months before the second subject is enrolled, after which, should there be no serious safety concerns, parallel enrollment will be permitted. The study is recruiting subjects, and has been registered at http://www.clinicaltrials.gov (PCC# 121657).

Potential subjects are recruited for the study via distribution of flyers to staff at GLA Mental Health Outpatient programs. Flyers include summarized inclusion and exclusion criteria. Potential subjects are informed about the study by their treating clinician, and given contact information for the study psychiatrist and neurosurgeon if they are interested. Charts of potential patients are then reviewed by investigators based on an IRB-issued Waiver of Consent for Screening. Patients meeting chart-review-based inclusion and exclusion criteria are invited to attend an in person assessment for further determination of eligibility. Eligible subjects will sign informed consent. After this, they will undergo baseline evaluations spaced over a six-week period, including neuropsychological testing and a baseline ^18^FDG PET scan (described below). Patients are reassessed with the Clinician Administered PTSD Rating Scale (CAPS[154]) at the end of this baseline period, and only those who maintain a total CAPS score ≥85 and other inclusion and exclusion criteria will be kept in the study. An additional baseline evaluation is stipulated by California Law referring to ‘Psychosurgery’ (WIC Sec 5326.6): all potential subjects must undergo examination by an independent team, consisting of neurosurgeons and psychiatrists uninvolved in the treatment or the study protocol, to ascertain capacity to consent, severity of illness, and inadequacy of response to standard treatments. This team of independent experts is assigned by the Medical Director of the Los Angeles County Department of Mental Health. Concomitant psychotropic medication regimens will be kept constant for the first six months of the study, unless medication-related adverse events, intercurrent medical conditions, or changes in psychiatric status make alterations clinically necessary.

### Inclusion criteria

Inclusion criteria include the following:Male aged 25 to 70 years.Able to give informed consent in accordance with institutional policies and participate in the 2-year follow-up, involving assessments and stimulator adjustments.Patients must be stable on their current psychotropic medication for a period of 2 months before implantation and agree to not increase dosages or add any new medications for the first 6 months of the study, unless medically necessary.Chart diagnosis of chronic and treatment-refractory PTSD as the principal psychiatric diagnosis and cause of distress and social/occupational impairment.Confirmation of PTSD as the primary psychiatric diagnosis by the study psychiatrist via clinical interview and Clinician Administered Post-traumatic Stress Disorder Scale (CAPS) [154].Confirmation of combat trauma exposure via military record review and a Combat Exposure Scale (CES) [155] score ≥9.Minimum of 5-year total illness duration, with no 6-month period of clinical remission during the 5 years prior to entry in the study.Clinical record documentation of nonresponse to at least 2 of the following antidepressants, alone or in combination, at maximally tolerated FDA recommended doses for ≥6 months: sertraline, paroxetine, fluoxetine, citalopram, escitalopram, amitriptyline, imipramine, nortriptyline, desipramine, clomipramine, phenelzine, tranylcypromine, venlafaxine, mirtazapine. Antidepressant trials must include at least one SSRI and one SNRI or TCA at maximally tolerated FDA recommended doses for a minimum of 3 months.A minimum 3 month trial of prazosin at 10 mg per day or, if less, maximally tolerated FDA recommended doses, unless considered contraindicated based on co-morbid medical conditions or concomitant medications.Trial of at least 3 months of one of the following: lithium, divalproex sodium, carbamazepine, lamotrigine, olanzapine, risperidone, bupropion either alone or in conjunction with one or more of the agents in #8 and # 9 above.Six months of continuous individual psychotherapy, conducted at least twice monthly for minimum 45 minute sessions, and consisting of a) clinician-defined cognitive-behavioral psychotherapy directed toward reducing conditioned fear symptoms of PTSD; b) cognitive processing psychotherapy for PTSD [39]; c) prolonged exposure therapy for PTSD (imaginal, *in vivo*, and/or virtual reality) [47, 50]; or d) Eye movement desensitization and reprocessing therapy for PTSD including a trauma exposure component [40], with chart documentation of inadequate benefit despite concerted effort. Other forms of individual or group psychotherapy are permitted but not required for inclusion. (Patients who are unable to complete 6 months of psychotherapy may be included if the cause of treatment cessation was that the risks of further treatment, including intense psychological suffering, outweighed the potential benefits of continuing the treatment).All evidence based psychotherapy for PTSD (cognitive behavioral, cognitive processing, prolonged exposure, and eye movement desensitization) has been completed a minimum of 3 months prior to enrollment.Minimum baseline CAPS_17_ of 85 at entry, with a) scores of at least 4 (combined frequency and severity) on at least one symptom from each cluster (intrusion, avoidance and hyperarousal); b) score of 5 or more on CAPS_17_ items 4 or 5 (intense psychological distress or physiological reactivity on exposure to a reminder of the traumatic event); and c) no questionable validity (QV) rating greater than 1 on any CAPS item.Clinically significant impairment in occupational functioning due to PTSD, manifested by one or more of the following: a) Total federal (service connected ≥70%), or State (SSI) disability compensation for at least the past 2 years for PTSD; b) global assessment of functioning score ≤45; c) no period of full time gainful employment ≥3 months in the past 5 years.Clinically significant impairment in social functioning due to PTSD, manifested by one or more of the following: a) little or no social activity outside the household other than as necessary for medical appointments, practical matters such as grocery shopping, or to interact with other veterans; b) reliable description by a spouse or significant other, living with the patient, of repeated avoidance/refusal to participate in customary social engagements with friends, family or for recreational activities due to PTSD; c) two or more verbal or physical interpersonal altercations within the past year requiring another person’s intervention to prevent further escalation, or involving law enforcementCohabitation with a spouse or significant other adult person who a) can confirm the symptoms and impairment from PTSD and lack of significant symptomatic remission in the past 5 years; and b) is willing to participate with the study psychiatrist in answering questions for the life functioning in PTSD scale (LFIPS) at scheduled follow-up visits; and c) is willing to report unexpected adverse neurological or psychiatric events to study investigators and if advised by study investigators, assist the patient in accessing necessary services to address these.Willingness to have unexpected neurological or psychiatric symptom shared with the study psychiatrists and other study clinicians.Other medical conditions must be stable for at least 1 year, (conditions that require intermittent use of steroids or chemotherapy are excluded).

### Exclusion criteria

Exclusion criteria include the following:Suicide attempt in the last 2 years and/or presence of a suicide plan (an answer of ‘Yes’ to Question C4 in Section C-Suicidality of MINI International Neuropsychiatric Interview) [156].Psychosis or bipolar disorder; significant acute or ongoing risk for violence.Patients primarily diagnosed with DSM-IV-TR Axis I disorder other than PTSD as determined by the MINI.Within the 3 months prior to enrollment, subject has started a new psychotherapy program.Alcohol or illicit substance use disorder within the last 6 months, unstable remission of substance abuse, or chart evidence that comorbid substance use disorder could account for lack of treatment response.Current significant neurological conditions, including epilepsy, stroke, movement disorder; history of serious head injury with loss of consciousness.Patients with uncontrolled medical conditions (such as hypertension, diabetes, and infection).Uncontrolled chronic pain.Baseline Montgomery Asberg Depression Rating Scale (MADRS) [157] of ≥28.Patients who are receiving anticoagulation therapy.Significant abnormality on preoperative structural brain MRI.Electroconvulsive therapy (ECT) in the past 6 months.Contraindications to MRIs or the need for recurrent body MRIs.Immunosuppression.Patients who are not appropriate candidates for general anesthesia and/or DBS surgery.Current pursuit of new or increased disability compensation for PTSD.Has cardiac pacemaker/defibrillator, implanted medication pump, intracardiac lines, any intracranial implants (aneurysm clip, shunt, cochlear implant, electrodes) or other implanted stimulator.Patient has had past cranial neurosurgery.Patient unable to discontinue therapeutic diathermy.Use of other investigational drugs or psychotropic herbs within 30 days of baseline.Patients suffering from a neurovascular condition or other intracranial process.Patients suffering from a condition associated with a significant cognitive impairment.

An inclusion criterion perhaps somewhat unique to this study is the required participation of a cohabiting significant other for the duration of the study. The purpose of this aspect of the trial is first for safety purposes. We know that electrical stimulation of the amygdala has the potential to cause changes in emotional, perceptual, and behavioral functioning that subjects may not be completely aware of, be able to describe, or be able to remember. Given that this is the first attempt to target the amygdala with long-term stimulation in patients with PTSD, we felt it important to include an observer who knows the subject and is with them most of the time to increase sensitivity for detecting significant, unexpected adverse psychological or behavioral effects. To further explain this role to the significant other, an information sheet will be provided that details specific symptoms to look for, along with urgency of reporting and contact information of the investigators as well as emergency resources. Second, we believe from our own clinical experience that in many combat veterans, PTSD often affects interpersonal, family, and relationship functioning in ways that are perceived differently by veterans and their family members. Thus, we have constructed a scale for monitoring changes in interpersonal, social, and family functioning that permits assessment of patient functioning from the perspective of the patient and caregiver independently: the Life Functioning in PTSD Scale (LFIPS) [see Additional file2]. No data concerning the significant other will be collected. Furthermore, the loss of the significant other during the trial will not lead to the exclusion of the subject.

### Baseline assessments

The following baseline assessments will be completed over an extended 6-week baseline period after patients have given informed consent for inclusion, but before deep brain stimulator implantation:demographics,medical history (includes family history),medication history,physical exam,neurological exam,lab screening including urine toxicology,12 lead EKG,MRI scan (to exclude brain abnormalities),Mini International Neuropsychiatric Interview (MINI),Combat Exposure Scale (CES),Clinician Administered PTSD Scale (CAPS),Hamilton Anxiety Rating Scale (HAM-A),Montgomery-Asberg Depression Rating Scale (MADRS),Young Mania Rating Scale (YMRS),Global Assessment of Functioning (GAF),Clinical Global Impression of Severity & Improvement (CGI-S, CGI-I),Davidson Trauma Scale (DTS),Columbia-Suicide Severity Rating Scale (C-SSRS),Veterans Quality of Life Assessment (SF-36v),Life Function in PTSD (LFIPS) (Additional file 2),fluorodeoxyglucose (FDG) positron emission tomographic (PET) brain imaging,Amygdala DBS in Post-traumatic Stress disorder Scale (ADIPS) neuropsychological tests (Additional file 3)neuropsychological battery (Additional file 4), andelectroencephalogram (EEG), 30 min awake and sleep.

### Randomization and blinding

There will be two study groups, A and B, corresponding to either onset of active stimulation at 30 days or 90 days post-implantation. Prior to enrollment of the first patient, a computer algorithm will randomize each of the six potential subjects to either group A or B (three each), in blocks of two. After the 1-month post-implantation EEG telemetry session, the study neurophysiologist will learn the group assignment of each subject. Subjects and all other investigators will be blind to group assignment until completion of the trial.

### Outcome measures

The following measures will be used to assess symptomatic and functional outcomes [see Additional file1 for detailed description of measures 1 to 4]:PTSDClinician Administered PTSD Scale (CAPS) [154] Davidson Trauma Scale (DTS) [158]Other psychiatric symptomology/morbidity Montgomery-Asberg Depression Rating Scale (MADRS) [157]Young Mania Rating Scale (YMRS) [159]Columbia-Suicide Severity Rating Scale (C-SSRS) [160]Hamilton Anxiety Rating Scale (HARS) [161]Functioning/quality of lifeGlobal Assessment of Functioning (GAF) [162]Veterans Quality of Life Assessment (SF-36 V) [163]Life Function in PTSD (LFIPS) [see Additional file 2]Global outcomeClinical Global Impression of Severity and Improvement (CGI-S & CGI-I) [164]Neuropsychological measuresAmygdala Deep Brain Stimulation in PTSD Scale (ADIPS) [see Additional file 3]. Given that amygdala DBS has not previously been performed in humans with PTSD, we will also administer a unique neuropsychological battery, the Amygdala DBS in PTSD Scale (ADIPS), which was developed for this study. This battery is designed to systematically assess effects of electrode insertion and stimulation on cognitive, perceptual, emotional, and behavioral functions known to be influenced by the amygdala and its connections.Neuropsychological Battery [see Additional file 4]. This battery consists of standardized measures of attention, concentration, mental effort, verbal and nonverbal memory, language, visuospatial abilities, and executive skills. It will be administered at baseline and at 6, 12, and 24 months postimplantation by a certified neuropsychologist (RM).Functional neuroimaging. Preoperatively, patients will undergo a provocative PET-CT scan using fluorodeoxyglucose F-18 (FDG) to determine the baseline activity of the amygdalae, insulae, cingulate and mPFC regions as in previous studies [109, 110]. The PET procedure will include both a resting baseline study, and a second ‘stimulus provocation study’, during which patients will listen to an audio recording of a ‘trauma script’ made prior to the scanning session. The script will consist of the patient’s recitation of a narrative of the trauma that caused PTSD as in prolonged exposure therapy (for example, [47]). Study Psychiatrists (RK, HS) will be present during the PET session to ‘titrate’ symptom severity to moderate, but not intolerable levels of arousal. The same ^18^FDG PET scan paradigm will be repeated at 15 months postoperatively with optimal DBS programming parameters. Since patients enrolled in this study have failed psychotherapy, including exposure-based therapy, we expect that changes in amygdala activation observed on the second PET scan will not be the result of therapeutic habituation from the first exposure session, but rather the effect of DBS. We will compare ^18^FDG PET metabolism in the target regions between resting and stimulus-exposed conditions, and differences from preoperative to approximately one year after chronic DBS. Our data analysis of the PET scans will follow the described theory of parametric mapping using SPM (Wellcome Trust Centre for Neuroimaging) [165]. With this software, the PET data in each voxel will be normalized and fitted in a linear statistical model. Following the technique described by Shin and others [102], our hypotheses will be evaluated as contrasts where the linear compounds of the model parameters will be evaluated with t-tests. This data is then transformed into a z-score. Since we have strong directional hypotheses (that DBS reduces amygdala hyperactivity in PTSD patients), we will consider z >3.09 (*P* <0.001 one tail, cluster level) as a statistically significant difference. In this study, MM and DS will conduct and analyze the PET scans.Electroencephalographic changes. After the one-month post-implantation EEG telemetry session, patients will have routine EEGs performed monthly for 15 months, and then every three months for the last nine months of the study. These will be analyzed by our study neurologist, JC, with particular attention paid to development of epileptiform changes.

Study assessments will occur weekly for five months after implantation, monthly for ten months, then every three months for the final nine months. All study measures will be completed at baseline, and then repeated as follows (see Additional files1,2,3 and4 for detailed descriptions, and Additional file5 for overall study timeline):Clinical monitoring and system status check at each visit.Stimulator adjustments, CAPS, MADRS, YMRS, C-SSRS, LFIPS, ADIPS, CGI, vital signs, and EEG monthly for 15 months, then every three months for nine months.GAF, SF-36 V, DTS, HAMA, ECG every three monthsNeuropsychological test battery at 6, 12, and 24 monthsResting and trauma script provoked PET Scan at 15 months

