The study includes two specific elements that hope to add to the understanding of brain-behavior relationships from our intervention. First, the double-blind staggered-onset sham-stimulation phase will allow us to observe changes associated with electrode implantation without electrical neuromodulation; what others have referred to as a ‘microlesioning effect’. This will also allow us to separate out nonspecific aspects of study involvement from specific effects of DBS. The study also includes prestimulation and poststimulation PET scanning sessions, each of which includes scans done before and after exposure to a trauma narrative as has been done in other functional neuroimaging studies of PTSD. We chose to use the ^18^FDG PET paradigm because it permits assessments of change in stimulus-driven functioning of the brain for longer time epochs than either ^15^O_2_ PET or fMRI. We feel that this more closely models the clinical difficulty patients with PTSD face; it is not just the nature and intensity of reactions, but their duration and ensuing effect on functioning that is important. We considered including a pre-implantation, as well as a pre-stimulation, post-implantation PET study. While this would be ideal from a scientific perspective, we decided that the additional patient burden was not justified given the completely uncharted territory of this pilot investigation.

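### Steering arousal to a moderate level in the script-provoked PET scan at both time points biases the provoked pre-to-post contrast toward no DBS effect

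*Protocol article*

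**What the plan says.** The functional neuroimaging item under Outcome measures in the Protocol article describes a resting FDG PET scan and a second scan during which the patient hears a recording, made beforehand, of his own trauma narrative. Study psychiatrists attend to titrate "symptom severity to moderate, but not intolerable levels of arousal". The "FDG PET scan paradigm will be repeated at 15 months postoperatively with optimal DBS programming parameters", with no exception stated for the titration step.

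Metabolism in the target regions is then compared "between resting and stimulus-exposed conditions, and differences from preoperative to approximately one year after chronic DBS". The directional hypothesis is "that DBS reduces amygdala hyperactivity in PTSD patients", judged at z > 3.09, one-tailed P < 0.001. The same item expects that change seen at the second scan "will not be the result of therapeutic habituation from the first exposure session, but rather the effect of DBS".

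Three other places bear on this:
- The Background section on targeting the amygdala says that amygdala signal in PTSD rises with symptom severity.
- The Discussion chooses FDG because "it permits assessments of change in stimulus-driven functioning of the brain" over longer epochs, and treats both the intensity and the duration of reactions as important.
- Study aims lists change in brain metabolism, from before implantation to 15 months, as the third aim.

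**The concern.** To learn whether stimulation lowers the brain's reaction to a trauma cue, the cue should be comparable at both scans and the reaction left free to differ. The text instead sets a target for the reaction. If stimulation makes a patient less reactive, bringing both sessions toward the same moderate level removes part of the difference that the contrast is meant to show. On the protocol's own premise that amygdala signal follows symptom severity, this conditions on a variable that lies on the path from treatment to outcome.

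At stake is the interpretation of the provoked scans. A small or absent provoked difference could mean that stimulation does little, or that titration hid its effect. Later analysis cannot recover the response to a fixed cue from scans acquired at adjusted arousal, and each of the six patients has only one pre-operative provoked session.

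**Working it through.** **The plan's own figure.** The one-sided 0.001 normal quantile is 3.0902, and 1 − Φ(3.09) = 0.00100. The stated threshold reproduces. No PET effect size, power or expected arousal is given, so everything numerical below is illustration on assumed inputs.

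**Model.** Let A0 and A1 be the arousal that the script would produce untitrated before surgery and at month 15, and T the moderate target. Titration moves arousal a fraction ρ of the way to T. The provoked amygdala signal is b × arousal, plus at month 15 any direct effect δ of stimulation at a given arousal.

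- Titrated arousal: A + ρ(T − A) at each scan.
- Visible change: b(1 − ρ)(A1 − A0) + δ.

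The arousal-driven part shrinks by the factor (1 − ρ); δ does not. The change in provoked minus rest inherits the same shrinkage, because the resting scan is not titrated.

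**Worked case.** Assume A0 = 8, T = 5 and a true cut of 50%, so A1 = 4 and the true fall is 4. Take ρ = 0.5 and δ = 0.
- Two-way titration: 8 becomes 6.5 and 4 becomes 4.5. The visible fall is 2.0, and 2.0/4 = 50%.
- Ceiling only (arousal is lowered when above T, never raised): 8 becomes 6.5 and 4 stays 4. The visible fall is 2.5, and 2.5/4 = 63%.

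**Simulation over patients** (baseline mean 8, SD 1.5; T = 5; true cuts of 20%, 30% and 50%; δ = 0). Share of the true fall that stays visible:

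| ρ | Two-way | Ceiling only, range over the three cuts |
|---|---|---|
| 0 | 100% | 100% |
| 0.5 | 50% | 53–63% |
| 0.8 | 20% | 24–41% |
| 1.0 | 0% | 5–26% |

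The ceiling still shrinks the contrast because the higher pre-operative response is cut more than the later one. That requires pre-operative arousal to exceed the ceiling more often than month-15 arousal does. This is plausible here, since the inclusion criteria demand a score of at least 5 on a CAPS item for distress or physiological reactivity to reminders.

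**What shrinkage does to detection.** A paired t-test with n = 6 and one-sided 0.001 serves as a rough stand-in for the SPM analysis. The critical value on 5 df is 5.893, so the smallest observed standardised difference that passes is 5.893/√6 = 2.41. The spread of the differences is held fixed; if titration also narrows it, the loss is smaller.

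| Assumed true effect | Power, full effect | Half | One fifth |
|---|---|---|---|
| 3.0 | 0.80 | 0.18 | 0.015 |
| 2.0 | 0.38 | 0.056 | 0.007 |

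**The attribution sentence.** It rests on failed psychotherapy, including exposure-based therapy. The inclusion criteria also admit patients who could not complete six months because the risks of continuing outweighed the benefits. Clinician-defined cognitive-behavioural therapy satisfies the criterion without exposure being specified. Under Design of the study, every subject is on active stimulation from three months, so month 15 has no unstimulated comparison against which habituation could be judged.

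**The case against.** The strongest reply is that the text describes a tolerability safeguard. The stimulus is a fixed recording, the word for titrate stands in quotation marks in the article, and nothing says that provocation is increased at month 15 until arousal is moderate. This limits the size: the plan states an aim and does not show that arousal ends up equal. It does not remove the bias, because a ceiling alone pulls the same way.

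A second reply is that the proposed mechanism is direct inhibition of the basolateral nucleus, so a fall in signal at matched arousal would remain visible. That stands; it is the δ term above, and it means that even complete titration need not bring the contrast to zero.

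Third, script timing, prompts and logging belong in an imaging manual. Their absence from an article is indeed no finding. The point rests on the stated procedure.

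A reader might infer more than the documents support:
- **That the third aim cannot be answered.** It can in part. The aim concerns brain metabolism generally, a resting scan is taken at both times, and the Background cites raised resting amygdala activity in combat PTSD. Nor does the protocol rank the provoked contrast above the others.
- **That inclusion accepts any psychotherapy.** It does not. Other forms are allowed but do not meet the criterion, and the Background says that prolonged exposure, cognitive processing therapy and EMDR all contain exposure. Only non-completers and clinician-defined cognitive-behavioural therapy leave exposure uncertain.
- **That the psychiatrists' knowledge of stimulation at month 15 is a separate flaw.** Any comparison of pre-implantation with month 15 is open in this design, and the scans are conducted and analysed by other staff.

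Habituation is a distinct matter: it would exaggerate an apparent DBS effect, the opposite direction to titration.

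**Conclusion.** The point holds for the script-provoked PET contrasts. As written, the procedure steers at both scans the response that stimulation is meant to change, and so biases the provoked pre-to-post difference and the change in provoked minus rest toward no effect. The direction rests on two things: the protocol's premise that amygdala signal tracks symptom severity, and titration working either two-way toward a common level or as a ceiling that binds more often before surgery.

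The size cannot be fixed from the document. The percentages and powers above show only how a given degree of titration would act. The resting pre-to-post comparison, the safety outcomes and the CAPS are untouched. This is worth correcting before scanning, but it does not threaten the trial's main purpose.

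**What to change.** - Use the same recording for the same planned duration at both scans, with no upward adjustment of provocation at month 15.
- Leave the psychiatrists' discretion to reduce or stop the exposure for safety unchanged at both sessions.
- Log every departure from the planned exposure, and record arousal ratings at fixed times in both sessions.
- Report the provoked contrast with these data, beside the resting contrast.
- Soften the attribution sentence: change at month 15 would be consistent with a DBS effect, but habituation cannot be excluded without an unstimulated comparison and with psychotherapy non-completers eligible.

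The cost is some procedure wording and a short log form. Arousal at month 15 may be lower than before surgery, which is itself a result.
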